#### Study visits 1–4.

Each study visit follows an identical three-day protocol. Approximately one week before the schedule visit, study staff will contact the participant to confirm that there have been no changes in health status and that menstrual cycles remain regular. Participants will be asked to provide the date of their most recent menstrual period to ensure that the visit falls within their assigned follicular or luteal phase. They will also be reminded to abstain from recreational drug use during the week leading up to the MRI session. The three-day protocol will be as follows:

Day 0: Participants will undergo a pregnancy test and will be instructed to take 5 mg of oral OLA (or PL) at night at their home between 9:30 and 11:30 pm.

Day 1: Participants will receive a standardized mixed meal (with vegan and vegetarian options) to be consumed at their usual dinner time or no later than 9:30 pm. This will serve as their final meal of the day, after which they must remain fasted until completing the study visit the next day. On the night of Day 1, participants will take 10 mg of oral OLA (or PL) before bed between 9:30–11:30 pm.

Day 2: Participants will be picked up by taxi from their home and brought to CAMH for the primary study assessments to occur. Participants will first undergo fasting bloodwork to measure glucose, insulin, c-peptide, estrogen, progesterone, LH, FSH, and OLA levels. Blood glucose, insulin, and c-peptide will be measured again after the MRI session. The visit includes two MRI scans: INP will be administered before MRI Scan #1 (approximately 30 minutes), followed by INI prior to MRI Scan #2 (approximately 30 minutes). MRI will be performed using CAMH’s research dedicated 3.0 Tesla GE scanner equipped with a 32-channel head coil. The scanning protocol will include a high-resolution T1-weighted structural image and a functional MRI (fMRI) scan to measure resting state brain activity.

Cognitive assessments will be conducted following the administration of both INP and INI, and will include the Brief Visuospatial Memory Test–Revised from the Kaplan Functional System [46] as well as the Digit Symbol Substitution Test [47] Participants will also complete a series of questionnaires and rating scales, including the 3-day food diary, the Food Craving Scales, the Profile of Mood States (POMS) [48], the Subjective Wellbeing Under Neuroleptics (SWN) [49], the Barnes Akathisia Rating Scale (BAS) [50], and the Stanford Sleepiness Scale (SSS) [51]. Anthropometric measures will also be collected, including height, weight, waist circumference, and blood pressure.

The above procedures are repeated for a total of 4 research visits (two of which will occur during the follicular phase and two during the luteal phase).

### Data analysis

#### MRI analysis.

The rsFC analyses, including pre-processing and denoising, will be conducted using a seed ROI-to-ROI approach implemented in the CONN toolbox (version 18b; https://www.nitrc.org/projects/conn). Functional images will be slice-time and motion corrected, realigned, co-registered to structural scans, normalized to MNI-space, and spatially smoothed with an 8-mm FWHM Gaussian kernel.

### Statistical analysis

The primary outcome is rsFC. Given the exploratory nature of this study, a formal power calculation was not performed. The sample size (N = 15) was instead informed by prior neuroimaging studies examining the effects of INI on MRI-derived outcomes, which have which have typically included 9–25 participants and reported large effect sizes (Cohen’s d: 0.8 to 1.4, f: 0.4–0.6). In the context of a within-subject crossover design, which reduces between-subject variability and increases statistical efficiency, this sample size is expected to provide adequate sensitivity to detect moderate-to-large effects in resting-state functional connectivity.

To address hypothesis #1, which is the difference in brain insulin sensitivity between cycle phases, analyses will be restricted to visits in which participants receive the oral PL. A linear mixed effects model will be conducted with rsFC as the dependent variable and fixed effects for intranasal condition (i.e., INI vs. INP), menstrual phase (follicular vs. luteal), and their interaction. Participant will be included as a random intercept, with age and BMI entered as covariates. The primary effect of interest is the intranasal condition x menstrual phase interaction, which tests whether the effect of INI (relative to INP) differs between follicular and luteal phases. Planned simple effects will assess (i) the effect of INI vs. INP within each phase, and (ii) the difference in INI-induced change (INI – INP) between phases.

To test the effect of OLA within each phase, a second linear mixed effects model will be conducted including all visits. Fixed effects will include intranasal condition (INI vs. INP), oral condition (OLA vs. PL), menstrual phase (follicular vs. luteal) and all interaction terms. Participants will be modeled as a random intercept, with age and BMI as covariates. The primary term of interest is the intranasal condition x oral condition x menstrual phase interaction, which tests whether OLA modifies INI-induced effects differently across cycle phases.

The primary analysis will be conducted according to the intention-to-treat (ITT) principle, including all participants enrolled in the study who have completed at least one study visit. This analysis will account for missing data under the missing at random (MAR) assumption using the maximum likelihood estimation within the linear mixed model’s framework. A per-protocol analysis will also be conducted as a sensitivity analysis, including only participants who completed the study with full adherence to the protocol, to assess the robustness of the primary findings.

All statistical analyses will be conducted using IBM SPSS Statistics Version 31 or R 4.3.2 (R Foundation for Statistical Computing, Vienna, Austria). The level of statistical significance will be set at α = 0.05 for all primary analyses, with corresponding confidence intervals reported where applicable. Adjustment for multiple comparisons will be applied as appropriate, using either Bonferroni correction or false discovery rate (FDR).

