### Study participants

This study will recruit fifteen healthy female volunteers aged 18–35 years, of any race or ethnicity, with normal body mass index (BMI 18.5–25 kg/m²) and regular menstrual cycles. Participants will be excluded from the study for the following reasons: 1) History of psychiatric illness (the Mini International Neuropsychiatric Interview (MINI) will be used to screen for psychiatric illness in the present or past), 2) Pre-diabetes or diabetes (fasting glucose ≥6.0 mmol/L, HbA1c>6% or use of any anti-diabetic drug), 3) Evidence of impaired insulin sensitivity, assessed using the Homeostatic Model Assessment for Insulin Resistance (HOMA-IR) ≥1.8 [42,43], 4) Family history of diabetes in a first degree relative (parent or sibling), 5) Use of weight reducing agents, 6) History of kidney or liver disease, 7) Moderate-to-severe substance use, 8) Irregular menstrual cycles (e.g., menstruation occurs less than 21 days or more than 35 days apart, or not having menstruated for three months (or 90 days), or conditions such as endometriosis or polycystic ovary syndrome (PCOS), or prior surgical interventions such as a hysterectomy or oophorectomy), 9) Use of hormonal birth control, 10) Current use of progesterone, estrogen, testosterone, or fertility treatment, 11) Pregnant or breastfeeding, 12) Major medical or surgical event within the last 6 months, 13) Any condition that interferes with safe acquisition of MRI data such as metal implants, pacemakers, cochlear implants, claustrophobia, etc., 14) Any contraindications to the investigational products as listed in the product monographs including known hypersensitivity to the drug or the excipients of the product (note: enzymatic lactose intolerance is NOT exclusionary), 15) Use of any of the prohibited medications listed in the product monograph of olanzapine (e.g., Levodopa and dopamine agonists and antihypertensive agents).

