### Recruitment status and study timeline

Recruitment for this study began in May 2024 and has been ongoing ever since. At the time of this submission, a total of 25 participants have consented to the study, 13 of which have been eligible and enrolled. Three participants dropped out at various stages of their participation, six have completed their full participation, and the remaining are still actively enrolled and completing study visits. The retention and successful completion of participants speak to the feasibility of the study being conducted in this population. Recruitment is currently ongoing and is anticipated to be completed by June 2026. Results and an associated publication are expected 6–12 months following trial completion.

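### The stated adequate sensitivity of N = 15 for moderate-to-large effects rests on simple insulin effects and does not hold for the two primary interaction terms

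*Protocol article*

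**What the plan says.** The protocol article (Study participants) sets the size: "This study will recruit fifteen healthy female volunteers". Its Statistical analysis section is open about the basis: "Given the exploratory nature of this study, a formal power calculation was not performed". N = 15 was informed by "prior neuroimaging studies examining the effects of INI on MRI-derived outcomes", with 9 to 25 participants each, which "reported large effect sizes" (d from 0.8 to 1.4, f from 0.4 to 0.6). After pointing to the within-subject design, the section concludes that "this sample size is expected to provide adequate sensitivity to detect moderate-to-large effects in resting-state functional connectivity".

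The same section then names the primary terms. For hypothesis 1, on the oral-placebo visits only, it is the INI × phase interaction. For the olanzapine question, on all visits, it is the three-way interaction of INI, oral condition and phase. Both models have a random intercept for participant and no other random effect. Simple INI-versus-INP effects within each phase are planned as well. Alpha is 0.05, with Bonferroni or FDR adjustment where appropriate. Incomplete participants are kept by maximum likelihood under missing at random.

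**The concern.** The effect sizes that support N = 15 describe one comparison, insulin against placebo spray. The primary terms are differences between such comparisons, and differences of differences. They carry more variance at the same N, so a size that suits the simple comparison need not suit the interactions. The text also moves from evidence of large effects to a claim about moderate-to-large ones, with nothing added to support the step.

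The interpretation of a null result is at stake. If adequate sensitivity is on record, a non-significant three-way term could be taken to show that olanzapine does not alter the insulin response, although the test would often miss such an alteration. Hypothesis 2 itself predicts no apparent olanzapine effect in the luteal phase, so the reading of null findings matters here.

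**Working it through.** The article gives no power or detectable effect, so there is no figure to reproduce. The check asks what N = 15 can detect for each contrast.

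**Inputs from the article.** N = 15; alpha 0.05; random intercept only; cited d of 0.8–1.4. The pattern comes from Objectives and hypotheses: an INI effect in the follicular phase, none in the luteal phase, and full removal of the follicular effect by olanzapine. Under this pattern each interaction contrast equals the follicular INI effect itself, the most favourable case the article describes. A partial difference would lower power.

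**Assumptions.** Two-sided test, no multiplicity adjustment, 80% power as the target, d = 0.5 as moderate. At first, d is the mean INI − INP change divided by the SD of that change.

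**Variance.** With residual variance s², one INI − INP change has variance 2s². Under a random intercept, changes at different visits are uncorrelated. The contrast variances are therefore:
- simple: 2s²/N
- two-way (difference of two changes): 4s²/N
- three-way (difference of two such differences): 8s²/N

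The noncentrality is d√(N/k), with k = 1, 2 and 4.

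**Degrees of freedom.** Per-participant contrasts give 15 − 1 = 14. The mixed models give 60 − 15 − 3 = 42 (four cells) and 120 − 15 − 7 = 98 (eight cells). Ranges below cover both choices.

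| Contrast, N = 15 | d for 80% power | Power at d = 0.5 | Power at d = 0.8 | Power at d = 1.4 |
|---|---|---|---|---|
| Simple INI − INP | 0.74–0.78 | 0.44–0.47 | 0.82–0.86 | above 0.99 |
| INI × phase | 1.05–1.10 | 0.25–0.27 | 0.53–0.57 | 0.95–0.96 |
| INI × oral × phase | 1.46–1.56 | 0.15–0.16 | 0.30–0.34 | 0.71–0.77 |

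With 14 df the three thresholds are 0.778, 0.778 × √2 = 1.10 and 0.778 × 2 = 1.56. So N = 15 fits a simple contrast at the bottom of the cited range.

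**If d is on the raw-score scale.** The threshold is multiplied by √(2(1 − ρ)), where ρ is the within-person correlation between cells. The article does not give ρ.

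| ρ | INI × phase | INI × oral × phase |
|---|---|---|
| 0.3 | 1.24–1.30 | 1.73–1.84 |
| 0.5 | 1.05–1.10 | 1.46–1.56 |
| 0.7 | 0.81–0.85 | 1.13–1.21 |
| 0.8 | 0.66–0.70 | 0.92–0.98 |

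For 80% power at a raw-scale d of 0.5, ρ must be about 0.89 for the two-way term and 0.94 for the three-way term.

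**If changes correlate across visits.** The planned model does not allow for this. A correlation of 0.5 between change scores would multiply the first set of thresholds by √0.5, giving 0.78 and 1.10 (14 df).

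**Multiplicity.** As an illustration, Bonferroni over 10 ROI pairs (alpha 0.005) raises the thresholds at N = 15 to 1.40–1.55 (two-way) and 1.92–2.20 (three-way), with d as the standardised change.

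**Attrition scenario.** Recruitment status and study timeline reports 3 dropouts among 13 enrolled. If the same fraction of 15 stayed, 15 × 10/13 = 11.5, about 12, would remain. At N = 12 the thresholds are 1.18–1.26 (two-way) and 1.64–1.78 (three-way).

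**The case against.** The strongest defence has four parts.

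1. **The study is declared exploratory and claims no power calculation.** This stands as an excuse for having no power figure. It does not support an affirmative statement that sensitivity is adequate.

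2. **The sentence speaks of effects in connectivity, not of interactions, and simple effects are also planned.** In part this stands. For a large simple effect the statement is fair (power 0.82 at d = 0.8). At a raw-scale correlation of 0.8, a simple effect of 0.5 also reaches 81%. But the sentence is the only justification of N, and the terms the same section calls primary are interactions.

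3. **The thresholds depend on a correlation the article does not give.** This stands, and it is why a range is needed. A reader might infer that both interactions need effects at or above the top of the cited range. The documents do not support that. The two-way threshold of 1.05–1.10 lies inside 0.8–1.4, and the three-way threshold falls below 1.4 at raw-scale correlations of 0.7–0.8. At 0.8 the two-way threshold of 0.66–0.70 is even below the cited range. Neither interaction reaches 0.5.

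4. **Twelve completers is not a fixed ceiling.** A reader might subtract the dropouts ("Three participants dropped out at various stages of their participation, six have completed their full participation") from fifteen and conclude that at most 12 can complete. The article does not say whether dropouts are replaced or counted within the fifteen, and the planned analysis keeps partial data. Twelve is a scenario only.

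Nor does the article say that a null interaction would be read as evidence of no effect, and it already plans confidence intervals where applicable. The risk lies in what the sensitivity sentence invites.

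**Conclusion.** The concern holds in limited form. The sensitivity sentence is supported for a large simple INI − INP effect and is not supported, as worded, for either primary interaction. With d as the standardised change, the two-way term has about one chance in four of detecting d = 0.5 and a little over one in two at d = 0.8. The three-way term has about 15% and 30–34%, so it would miss an effect at the bottom of the cited range about two times in three. Only the three-way threshold passes the top of that range, and only narrowly.

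These figures rest on the hypothesised all-or-nothing pattern, the random-intercept model, two-sided unadjusted alpha 0.05 and 15 participants with complete data. Higher within-person correlation improves them. Partial effects, attrition and multiplicity adjustment worsen them. That moderate effects are out of reach for the interactions holds throughout the correlations from 0.3 to 0.8.

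**What to change.** Revise the sensitivity sentence in Statistical analysis:

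- Limit the claim of adequate sensitivity to large simple INI − INP effects, and drop the word moderate for the interactions.
- State the detectable effect at 80% power for each contrast, with its assumptions. At N = 15, unadjusted, with d as the standardised change, these are about 0.78 (simple), 1.05–1.10 (two-way) and 1.46–1.56 (three-way). Add the raw-scale range over assumed correlations; at 0.7–0.8 this is about 0.66–0.85 (two-way) and 0.92–1.21 (three-way).
- Note that multiplicity adjustment raises these values.
- If 12 completers are shown, label them an attrition scenario (two-way about 1.2–1.3, three-way about 1.6–1.8).
- State that a non-significant interaction will be reported with its confidence interval as inconclusive, not as evidence of no effect.

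This changes text only. It needs no added participants and no change to the models or to conduct. The cost is a less favourable stated sensitivity.

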## Objectives and hypotheses

In this study, we seek to address a significant gap in the literature by investigating 1) how brain insulin action differs in females according to their menstrual cycle phase, and 2) how a high metabolic liability agent such as OLA might interrupt these differential insulin effects. We have chosen to conduct this study in healthy volunteers to minimize confounding effects of psychiatric disorders on glucose metabolism [36]. OLA was selected as a representative antipsychotic due to its well-established metabolic liability [37]. An acute dosing paradigm (i.e., two days of dosing) is employed to avoid longer-term changes in adiposity [38]. thereby allowing for a more precise assessment of whether antipsychotics exert direct effects on brain insulin function.

Resting state functional activity and connectivity (rsFC) will be used as a neural signature of brain insulin action. We hypothesize that 1) INI, but not intranasal placebo (INP), will modulate resting state activity in the brain in females during the follicular phase of their menstrual cycle but not the luteal phase; 2) Oral OLA will inhibit all INI-induced effects, relative to oral placebo (PL) during the follicular phase. OLA will have no apparent effect in the luteal phase given pre-existing brain IR.

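### The stated sensitivity of N = 15 to moderate-to-large effects is not supported for the two primary interaction terms, above all at the moderate end

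*Protocol article*

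**What the plan says.** All of this is in the Statistical analysis section of the protocol article, except the hypotheses.

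- On planning: "Given the exploratory nature of this study, a formal power calculation was not performed". The text continues: "The sample size (N = 15) was instead informed by prior neuroimaging studies examining the effects of INI on MRI-derived outcomes".
- On the evidence: those studies are described as having "reported large effect sizes (Cohen’s d: 0.8 to 1.4, f: 0.4–0.6"). The article does not say which contrast these values describe or which SD they are scaled by.
- On the result: after citing the efficiency of a within-subject crossover, it concludes that "this sample size is expected to provide adequate sensitivity to detect moderate-to-large effects in resting-state functional connectivity".
- On hypothesis 1 (placebo visits only): "The primary effect of interest is the intranasal condition x menstrual phase interaction".
- On olanzapine (all visits): "The primary term of interest is the intranasal condition x oral condition x menstrual phase interaction".
- On the expected pattern (Objectives and hypotheses): INI "will modulate resting state activity in the brain in females during the follicular phase of their menstrual cycle but not the luteal phase". Olanzapine is expected to remove the INI effects in the follicular phase and to do nothing apparent in the luteal phase.

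No effect size is given for either interaction.

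**The concern.** The benchmark and the tests differ in kind. The effect sizes come from "prior neuroimaging studies examining the effects of INI on MRI-derived outcomes". The first primary term is a difference between two INI-INP changes, and the second combines four of them. Each added difference adds variance. Under the article's own hypotheses it adds no signal, because the other changes are expected to be zero. A sample that suits one INI-INP change need not suit either interaction, and the article does not make that step.

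What is at stake is how a null result is read. If the article says the design can see moderate effects, a non-significant interaction invites the conclusion that cycle phase does not matter, or that olanzapine does not interfere with insulin action. At the low end of the cited range, under the assumptions below, the three-way test would miss the predicted effect about two times in three.

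**Working it through.** **No figure to reproduce.** The article states no power, target or formula. The 80% target used here is an assumption.

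**Inputs from the article.** N = 15, each participant measured in all eight intranasal x oral x phase cells; alpha 0.05 (taken as two-sided); cited d of 0.8 to 1.4; a random intercept for participant; the hypothesised pattern above.

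**Assumptions.** All 15 sets are complete, with no multiplicity correction. Moderate means d = 0.5, by convention. In the main calculation d is scaled by the SD of the INI-INP change, s, and changes are independent across visits, as a random-intercept model implies.

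**Contrasts.** Let D be the INI-INP change at a visit. Only the follicular placebo visit has a non-zero mean, d x s.

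- Simple effect: D. Mean d x s, SD s. Non-centrality d√15.
- INI x phase: D(follicular, placebo) − D(luteal, placebo). Mean d x s, SD √2 s. Non-centrality d√(15/2).
- INI x oral x phase: difference of two such differences. Mean d x s, SD 2s. Non-centrality d√(15/4).

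At d = 0.8 these are 3.10, 2.19 and 1.55.

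Power comes from the non-central t. The lower figure of each range uses 14 df. The upper uses the mixed-model residual df: 60 − 15 − 3 = 42 for the first model and 120 − 15 − 7 = 98 for the second.

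| d (SD of change) | Simple | INI x phase | INI x oral x phase |
|---|---|---|---|
| 0.5 | 44% | 25-27% | 15-16% |
| 0.8 | 82% | 53-57% | 30-34% |
| 1.1 | 98% | 80-84% | 51-56% |
| 1.4 | >99% | 95-96% | 71-77% |
| d for 80% power | 0.78 | 1.05-1.10 | 1.46-1.56 |

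N = 15 therefore fits a simple contrast at d = 0.8, which is not a primary term.

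**Changes correlated across visits.** A common correlation of 0.5 between the changes multiplies each interaction SD by √(1 − 0.5) = 0.71. With 14 df, the detectable d becomes 0.78 (two-way) and 1.10 (three-way). Power at d = 0.8 is 82% and 53%; at d = 0.5 it is 44% and 25%.

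**d on the raw-scan SD.** With scan correlation r, d on the change scale is d/√(2(1 − r)). At r = 0.5 this returns the table above. At r = 0.8, 0.5 becomes 0.79 and 0.8 becomes 1.26.

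| r | d | INI x phase | INI x oral x phase |
|---|---|---|---|
| 0.3 | 0.5 | 19-20% | 12-13% |
| 0.3 | 0.8 | 41-44% | 23-25% |
| 0.7 | 0.5 | 38-41% | 21-24% |
| 0.7 | 0.8 | 75-79% | 46-51% |
| 0.8 | 0.5 | 52-56% | 30-33% |
| 0.8 | 0.8 | 90-92% | 63-68% |

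For 80% power at a raw-scale d of 0.5, r must satisfy 0.5/√(2(1 − r)) ≥ 1.05-1.10 for the two-way term, so r of about 0.89-0.90. For the three-way term the bound is 1.46-1.56, so r of about 0.94-0.95. The article gives no correlation.

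**Direction of the remaining assumptions.** The pattern used is the most favourable within the hypotheses: no luteal INI effect and full inhibition by olanzapine. A smaller follicular-luteal difference, partial inhibition, dropout or a multiplicity correction would each lower these figures.

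**The case against.** The article is open that the study is exploratory and that no power calculation was done. That stands: nothing has been miscalculated, and calling this an arithmetic error would be wrong. The disclosure does not cover the sentence that follows it, which makes a positive claim about sensitivity.

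Three stronger readings are tempting, and the documents do not support them.

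- A reader might infer that the cited d values are known to be simple INI contrasts. The article says only that they are effects of INI. What can be said is that no interaction effect size is offered.
- A reader might infer that the design lacks the sensitivity claimed, without qualification. That goes too far for INI x phase: power is 80-84% at d = 1.1, the middle of the cited range, and 90-92% at d = 0.8 if d is on the raw-scan SD with r = 0.8. The three-way term also passes 80% at raw-scale d = 1.4 with r = 0.7 (90-93%).
- A reader might infer that even a simple INI-INP contrast cannot cover a moderate effect. It has 44% power at d = 0.5 on the change scale, but 81% if d is on the raw-scan SD with r = 0.8. Which applies cannot be settled from the article.

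Two further defences have some force. The crossover does gain efficiency, but the calculation already uses within-person contrasts. The sentence may also refer to effects in general, since simple effects within each phase are planned. If it means the interaction's own standardised effect, power is 82% at 0.8 but still 44% at 0.5, and the cited INI values are then not evidence for it. Finally, no passage says that a null will be read as absence of effect; that is a risk, not a stated plan.

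**Conclusion.** The concern holds in limited form, as a wording correction that should be made. It does not call for a change of sample size, model or type I error.

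- Moderate is unsupported for both primary terms. At d = 0.5 the best figures over the scenarios tried (scan correlation 0.3 to 0.8, or changes correlated 0.5 across visits) are 56% for INI x phase and 33% for INI x oral x phase.
- The three-way term is weak over much of the cited range. Under independence across visits it stays below 80% even at d = 1.4 (71-77%).
- The two-way term is adequate from d of about 1.1, or from lower values if within-person correlation is high.

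The exact figures rest on the declared assumptions about the standardiser, the correlation and the 80% target, none of which the article fixes. The mismatch does not: the evidence offered concerns effects of INI, and the terms named as primary are interactions.

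**What to change.** Keep N = 15. In the Statistical analysis section, replace the sensitivity sentence with detectable effects for the actual primary terms, assumptions included. For example: *With 15 complete sets, two-sided alpha 0.05 and no multiplicity correction, and if INI acts only in the follicular phase on placebo, 80% power needs an INI-INP effect of about 1.05-1.10 SD of the INI-INP change for INI x phase and about 1.46-1.56 SD for INI x oral x phase if changes are independent across visits, or about 0.78 and 1.10 SD if they correlate 0.5.* Alternatively, withdraw the sentence and let the exploratory statement stand alone.

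In either case, report both interactions as estimates with 95% confidence intervals, in line with the section's existing commitment to give intervals where applicable, and state that a non-significant interaction is inconclusive.

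The cost is text only, and the stated sensitivity becomes less favourable. The article reports recruitment as ongoing, so the change can be made before results are known.
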